## Abstract

**Background:** Population-based studies have consistently showed an increased incidence of coronary heart disease and cardiac mortality in patients with type 2 diabetes mellitus (T2DM). Tongmai Jiangtang capsules (TJC) are Chinese patent medicines that have been approved in China for the treatment of diabetic vascular complications. However, the evidence supporting the efficacy of Tongmai Jiangtang capsules in type 2 diabetic coronary heart disease (T2DM-CHD) remains unclear. Herein, we designed a randomized, parallel-controlled clinical trial to investigate a new complementary therapy for T2DM-CHD patients.

**Methods:** A total of 360 T2DM-CHD subjects (aged 18–75 years) will be randomly assigned to the TJC group or the placebo group at a 2:1 ratio. On the basis of western medicine therapy, all the participants will receive TJC or placebo, orally, three capsules/treatment, three per day for 12 weeks. The primary outcomes will be assessed according to the Canadian Cardiovascular Society (CCS) classification. All statistical analyses will be performed setting a two-sided 0.05 significance level, using SAS 9.4 statistical software.

**Discussion:** The efficacy of TJC for the treatment of T2DM-CHD patients will be evaluated. The study will provide reliable clinical research evidence for application of TJC in treating T2DM-CHD patients.

**Clinical Trial Registration:**
https://www.chictr.org.cn/enIndex.aspx, Chinese Clinical Trial Registry ChiCTR2000037491.

## Introduction

Type 2 diabetes mellitus (T2DM) is a common non-communicable disease worldwide. According to data from the World Health Organization, the worldwide prevalence of T2DM was 2.8% in 2000 and it is expected to rise to 4.4% in 2030 (Wild et al., 2004; Guariguata, 2012). The prevalence of T2DM is also increasing rapidly in China (Zhang et al., 2018a). T2DM is associated with a high risk of cardiovascular, microvascular, and other complications (Sarwar et al., 2010). Studies have shown that T2DM is an established risk factor for coronary heart disease (CHD) (Schramm et al., 2008) and can significantly increase the risk of death (Di Angelantonio et al., 2015).

At present, studies have shown that aspirin, statins, angiotensin-converting enzyme inhibitor (ACEI), angiotensin receptor blockers (ARB), and metformin can reduce the risk of vascular complications in patients with T2DM coronary heart disease (T2DM-CHD) (Holman et al., 2008; Malahfji and Mahmarian, 2018). Despite great progresses in treatment strategies for vascular disease in T2DM-CHD, some adverse reactions and side effects may occur, such as the risk of bleeding in the elderly caused by low-dose aspirin (McNeil et al., 2018), statin-related muscle symptoms (Stroes et al., 2015), and hyperkalemia caused by ACEI and ARB, especially in T2DM patients with chronic renal insufficiency (Raebel, 2012). There is a critical need for evidence-based novel therapies.

Traditional Chinese Medicine (TCM) has a thousand-year history and an analogous history of clinical practice, TCM has accumulated rich experience and plays a significant role in treating diabetes mellitus. As a complementary therapy, TCM is promising for the treatment of vascular complications in T2DM patients and is widely used in Asian countries. Tongmai Jiangtang capsules (TJC) produced by Baoding Tianhao Pharmaceutical Co. Ltd. (Baoding, China) gained approval by the China Food and Drug Administration (CFDA) (National Medicine permission number: Z20026853) in 2002. TJC consists of Radix Pseudostellariae, Radix Salviae Miltiorrhizae, Rhizoma Coptidis, Radix Astragali, Gynostemma pentaphylla, Rhizoma Dioscoreae, Rhizoma Atractylodis, Radix Scrophulariae, Hirudo, Fructus Malvae, and Radix Puerariae. As the main components in TJC, Radix Salviae Miltiorrhizae and Radix Astragali effectively increase coronary blood flow, relieve myocardial ischemia, and inhibit platelet aggregation (Zhang 2015). A systematic review of the efficacy and safety of Radix Salviae Miltiorrhizae combined with Radix Astragali treatment for CHD showed significant improvements among patients with regard to hemorheology, clinical efficacy, and frequency of angina episodes (Ma et al., 2021). Clinical studies have shown that TJC is remarkably effective for diabetic microvascular and macrovascular complications, such as diabetic peripheral neuropathy (Chen et al., 2015), diabetic nephropathy (Li et al., 2019), and diabetic cerebrovascular disease (An and Xiao, 2018). In our previous clinical study, we showed that TJC exerted therapeutic effects on improving cardiac function and exercise tolerance in T2DM-CHD patients, which implied that it could be considered as a potential Chinese-patent medicine for T2DM-CHD treatment. However, the current clinical data of TJC as complementary therapy in the treatment of T2DM-CHD still lacks high-quality clinical research evidence. Therefore, we designed a randomized, double-blinded, multi-center clinical trial to evaluate the efficacy of TJC in improving cardiac function and exercise tolerance in T2DM-CHD patients.

## Methods/Design

### Study Objectives

The purpose of this pilot study was to evaluate the efficacy of TJC in improving cardiac function and exercise tolerance in T2DM-CHD patients. We hypothesized that, combined with Western conventional medicines, TJC would be more effective than placebo in improving cardiac function and exercise tolerance in T2DM-CHD patients. If the hypothesis is true, this study will provide clinical evidence supporting TJC for the treatment of T2DM-CHD. A total of 360 eligible participants will be enrolled in this study over the course of 2 years.

### Study Design

This study was designed as a randomized, double-blinded, parallel controlled, multicenter clinical trial. A total of 360 eligible participants will be randomly divided into treatment group and control group in a ratio of 2:1. This study was prospectively registered with Chinese Clinical Trial Registry (ChiCTR2000037491) in September 2020. The study flow is shown in Figure 1.

**FIGURE 1 F1:**
[figure not shown]
Schedule of the trial. Abbreviations: T2DM- CHD, Type 2 diabetic coronary heart disease; TCJ, Tongmai Jiangtang capsules; CCS, Canadian Cardiovascular Society; FBG, fasting blood glucose; GH, glycosylated hemoglobin; SAQ, Seattle angina questionnaire; AE, adverse event.

### Setting and Participants

This study will be conducted at 5 research settings in China (The Affiliated Hospital of Shaanxi University of Chinese Medicine, The Second Affiliated Hospital of Shaanxi University of Chinese Medicine, The Second Affiliated Hospital of Zhejiang Chinese Medical University, Shaanxi Hospital of Traditional Chinese Medicine, and Xi’an Hospital of Traditional Chinese Medicine). Recruitment strategies will include publishing advertisements on local free papers, social media, online publications, and posters displayed in the five participating institutions. Recruitment began in October 2020 and will be completed within 2 years. Patients who consent to participate will be examined and diagnosed by associate chief physicians to confirm their inclusion in the study and will be registered on an online allocation system after written informed consent has been obtained.

### Eligibility Criteria

#### Diagnostic Criteria

Criteria for the diagnosis of T2DM-CHD refer to the Chinese Guidelines for the Prevention and Treatment of Type 2 Diabetes (2017) (Jia et al., 2019) and the Guidelines for the Diagnosis and Treatment of Stable Coronary Heart Disease in 2018 (Fihn et al., 2012). The diagnosis of T2DM generally precedes that of CHD, which appears as a complication of T2DM.

#### Inclusion Criteria

 ◆Male and female patients aged from 18 to 75 years, inclusively; ◆Patients satisfying the diagnostic criteria of T2DM-CHD, and have a T2DM disease course of more than 6 months; ◆Canadian Cardiovascular Society (CCS) classification ≥ II in the screening phase;◆Levels of glycosylated hemoglobin A1c (HbA1c) between 4.0 and 8.0%, inclusively, during the screening period;◆Provision of signed informed consent.

#### Exclusion Criteria

 ◆Type 1 diabetes mellitus, secondary diabetes or failure to specify which type of diabetes;◆Patients who have experienced severe hypoglycemic, ketoacidosis, or hyperosmolar coma within 3 months;◆Patients experiencing acute coronary syndrome within 3 months;◆Evidence of occurrence of cerebrovascular accidents, such as cerebral infarction and cerebral hemorrhage, within 6 months;◆History of combined severe heart failure (New York Heart Association class ≥Ⅲ), severe arrhythmia, and other heart diseases;◆Patients who have received TCM monotherapy or other TCM prescriptions for the treatment of T2DM and CHD within 14 days;◆Allergic constitution or previous allergy to multiple drugs, or known allergy to research drugs and/or its ingredients;◆Uncontrolled hypertension (systolic blood pressure [SBP] ≥180 mmHg and/or diastolic blood pressure [DBP] >110 mmHg) or hypotension (SBP <90 mmHg and/or DBP <50 mmHg);◆Patients presenting combined severe liver and kidney dysfunction (including patients undergoing dialysis), active liver disease (including primary biliary cirrhosis and unexplained persistent liver dysfunction), or malignant tumors;◆Any comorbidities that may affect the evaluation of efficacy and/or safety;◆Pregnant or lactating women and those who are planning a pregnancy during the trial or within 3 months after the cessation of the trial;◆Participation in other clinical studies within 3 months.

#### Withdrawal Criteria

 ◆Signs of exacerbation or deterioration clearly related to the intake of the study drug;◆Comorbidities, complications, adverse events (AEs), or serious AEs (SAEs) occurring during the study;◆Concomitant use of forbidden drugs or receipt of prohibited treatment potentially influencing efficacy and safety;◆Subjects who request to withdraw from the study;◆Poor compliance by subjects or the amount of drug used does not meet the regulations (less than 80% or more than 120%);◆Subjects who have reached the clinical recovery standard before the full course of treatment, and have applied for termination of medication.◆Blinding is uncovered or emergency unblinding is required.

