### Statistical Analysis

The statistical analysis plan will be specified before the final data analyses. The statistical analyses will be undertaken via Statistical Analysis System 9.4 (SAS Institute, Inc. Cary, NC) by the Department of Medical Statistics, at the National Center for Cardiovascular Diseases, Beijing. Data from all patients who undergo randomization will analyzed according to the intention-to-treat (ITT) principle. Consistent with the CONSORT statement and ITT principle, the last observation carried forward method will be used for missing values.

For quantitative data, we will calculate the mean, standard deviation, median, minimum, maximum, and interquartile range. For qualitative data, we will describe various frequencies or percentages. The student’s t-test will be used for quantitative data with normal distribution, while the Wilcoxon rank sum test will be used for quantitative data without normal distribution. The chi-square test or Fisher’s exact test will be used for qualitative data. We will analyze intra-group or inter-group differences before and after treatment. Concerning primary outcome, the effectiveness rate of patients whose CCS classification decreased ≥1 after 12 weeks of medication, the differences intra-group or inter-group will be compared using the CMH chi-square test adjusted for clinical site. We will include sex, center, baseline CCS classification, baseline HbA1c level, and baseline lipid levels as covariates in an analysis of covariance (ANCOVA) for statistical differences between groups by reducing the error variance. Statistical Significance will be assumed at a two-sided p-value less than 5%. The relative risk with corresponding 95% confidence interval (CI) to compare dichotomous variables will be calculated.

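### The withdrawal criteria do not separate stopping study drug from leaving the study; applied as study withdrawal, they lose Week-12 CCS for outcome-related reasons that ITT with LOCF cannot repair

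*Protocol article*

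**What the plan says.** The Withdrawal Criteria section of the protocol article is one undivided list. Besides drug-related deterioration and the subject's own request to leave, it contains:

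- "Comorbidities, complications, adverse events (AEs), or serious AEs (SAEs) occurring during the study", with no qualifier for severity, causality or the investigator's judgement;
- "Concomitant use of forbidden drugs or receipt of prohibited treatment potentially influencing efficacy and safety";
- poor compliance, or drug use below 80% or above 120%;
- "Subjects who have reached the clinical recovery standard before the full course of treatment, and have applied for termination of medication";
- "Blinding is uncovered or emergency unblinding is required".

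One item speaks of leaving the study and another of ending medication. The list does not say which consequence applies to the rest.

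Statistical Analysis states: "Data from all patients who undergo randomization will analyzed according to the intention-to-treat (ITT) principle". It adds that "the last observation carried forward method will be used for missing values".

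The primary outcome is the proportion of subjects whose CCS class falls by at least 1 at Week 12. In Table 1, CCS, the SAQ and nitroglycerin use are recorded at baseline and Weeks 4, 8 and 12. The treadmill test, fasting glucose, HbA1c and lipids are measured only at baseline and Week 12. Compliance is judged at Weeks 4, 8 and 12. The sample size section allows for 20% dropout.

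**The concern.** All these triggers occur after randomisation, and most plausibly track the outcome or the treatment. Deterioration and many adverse events go with worse angina; recovery goes with better angina. The Blindness section permits unblinding only after a 3-point MACE, so that trigger, when it arises by the permitted route, is tied to a cardiovascular event.

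If a site reads the list as reasons to leave the study, patients who meet a criterion before Week 12 have no Week-12 CCS, and the gaps depend on how they were doing. An ITT analysis keeps these patients in the denominator but must supply their outcome by rule. The estimate then depends partly on who was withdrawn and when, and this can differ between arms. Outcomes not collected cannot be recovered at the analysis stage.

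**Working it through.** **Inputs.** From Sample Size Calculation: 85% v 70% response, alpha 0.025, power 80%, 20% dropout, 240 + 120 patients. From Statistical Analysis: two-sided 5% test, ITT, LOCF. The withdrawal rates and carried values below are assumptions, because the article gives none by reason or by arm.

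**1. The plan's own figure.** Read alpha 0.025 as one-sided, which equals the two-sided 5% of the analysis. The unpooled formula gives, for placebo, n = (0.70×0.30 + 0.85×0.15/2) × (1.960 + 0.842)² / 0.15² = 95.5. Dividing by 0.8 gives 119.4, against 118 stated. The sample size is thus reproduced to within 2 placebo patients and is not itself at issue. The allowance is 20% of 240 = 48 and 20% of 120 = 24, or 72 of 360.

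**2. What LOCF does with a withdrawn patient.**
- Withdrawn before Week 4: only the baseline CCS exists. Its change is 0, so the patient is a non-responder by construction.
- Withdrawn after an improvement at Week 4 or 8: carried as a responder, whatever would have followed.
- Treadmill, glucose, HbA1c and lipids: with no value between baseline and Week 12, LOCF imputes no change for every patient withdrawn before the Week-12 tests.

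**3. Unequal withdrawal, no true effect.** Assume 70% response in both arms, withdrawal unrelated to response within arm, and non-response carried.
- 20% TJC, 10% placebo: 0.70×0.80 = 56% v 0.70×0.90 = 63%, a bias of -7 points.
- 10% TJC, 20% placebo: 63% v 56%, a bias of +7 points.

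**4. Equal withdrawal, planned effect.** With withdrawal w in both arms and non-response carried, the difference is 15 × (1 - w) points. Power is for 240 v 120, two-sided 5%, pooled variance under the null.

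| w | TJC v placebo | Difference (points) | Power |
|---|---|---|---|
| 0% | 85.0% v 70.0% | 15.0 | 90.4% |
| 10% | 76.5% v 63.0% | 13.5 | 76% |
| 20% | 68.0% v 56.0% | 12.0 | 61% |
| 30% | 59.5% v 49.0% | 10.5 | 47% |

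Dropping 20% of patients instead (192 v 96) gives 83.5% power. The 20% inflation covers that loss of numbers, not a dilution of the effect by carried non-responses.

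**5. Worst-case bounds at the planned 20% loss.** Take 85% v 70% among the 80% observed, and let the missing 20% be all failures or all responders.
- TJC: 0.8×0.85 = 68%, up to 68 + 20 = 88%.
- Placebo: 0.8×0.70 = 56%, up to 56 + 20 = 76%.
- Difference: 68 - 76 = -8 points, to 88 - 56 = +32 points.

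These are limits on what the missing data could hide, not expected biases.

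**The case against.** The strongest reply is that the document is a condensed article. It nowhere says that visits stop or that outcomes are discarded, and the full protocol may keep withdrawn patients in follow-up. That stands as far as it goes: loss of the Week-12 data is a consequence of one reading. But the list itself is stated here, mixes the two events and has an unqualified adverse-event item, so the point concerns a stated rule and not a silence.

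Four stronger readings are tempting and are not supported:

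- **That the criteria contradict ITT.** Statistical Analysis keeps every randomised patient and names a rule for missing values. What suffers is the follow-up on which an ITT analysis relies, not the analysis set. CCS at Weeks 4 and 8 also gives LOCF something to carry for later withdrawals.
- **That recovery or any prohibited drug is enough.** The recovery item also needs the subject's request to stop medication, and the prohibited-treatment item is limited to treatment that might affect efficacy and safety.
- **That adverse-event follow-up is cut short.** Safety Assessment requires every adverse event to be recorded, related or not, with its results and follow-up time.
- **That 20% loss can shift the difference by 20 points either way.** Twenty points is the full width of the range in one arm. Around the planned rates, TJC can move by -17 to +3 and placebo by -14 to +6, so the difference moves by -23 to +17.

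It is also fair to say that the 20% is total dropout. It includes withdrawal of consent, which no rewording prevents, and the article does not show how much would come from these criteria.

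**Conclusion.** The point holds in this form. The criteria do not separate stopping study drug from leaving the study. If they are applied as study withdrawal, Week-12 CCS is missing for reasons plausibly related to outcome, and ITT with LOCF does not correct that. The main secondary measures, including the treadmill test on which the exercise-tolerance objective depends, fare worse, because LOCF can only return their baseline value.

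The size depends on unknown withdrawal rates. Under the assumptions shown, a 10-point imbalance in withdrawal produces a 7-point bias, nearly half the planned 15. Equal 20% withdrawal carried as non-response takes power from 90% to about 61%. Early responses carried forward would push the other way, so neither the direction nor the amount can be predicted. The conclusion that the two sections need reconciling does not depend on these illustrations.

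**What to change.** Reconcile Withdrawal Criteria with Statistical Analysis by stating that:

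- meeting a criterion other than withdrawal of consent does not end follow-up;
- CCS, SAQ, nitroglycerin use, adverse events and the Week-12 tests are still collected at the scheduled visits and used in the ITT analysis;
- 80-120% compliance defines a per-protocol sensitivity set and is not a reason to end follow-up.

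Which events stop study drug is left to the sponsor; nothing here proposes a change to that.

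The cost is a short amendment, a note to the five sites, and the small burden of following off-drug patients to Week 12 at visits that Table 1 already schedules. It should be done while patients are still in follow-up. Some data will remain missing through withdrawal of consent, so a missing-data method is still needed, but for fewer patients.

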### Intervention

This is an add-on study protocol; all the participants will receive standard treatment. The interventions to be used are as follows: ◆Treatment group: TJC, 0.3 g/capsule, op, three capsules/per treatment, three times per day;◆Control group: TJC simulant, 0.3 g/capsule, op, three capsules/per treatment, three times per day.

With regard to standard treatment of CHD and T2DM during the intervention period, standard guidelines relative to aspirin, statin lipid-lowering drugs, ACEI or ARB, metformin, sodium-dependent glucose transporters 2 inhibitor, glucagon-like peptide-1 receptor agonists will be used. Substitution with TCM having similar composition and/or efficacy to TJC is not permitted. Researchers should record the concomitant medication truthfully, and maintain the dosage stability during the trial.

### Study Procedure

A time schedule of the study procedures is presented in Table 1. The study will include screening/baseline period and treatment period. The duration of the screening/baseline period will be 2 weeks, while the treatment period will be 3 months. Patients will be requested to provide informed consent in writing before the screening period following a full explanation of the study.

**TABLE 1 T1:** Study schedule.

Research phase	Screening/baseline	Treatment phase		
Number of visits	Visit 1	Visit 2	Visit 3	Visit 4
Visit time point	D-14–0	Week 4 ± 4 days	Week 8 ± 4 days	Week 12 ± 4 days
Data collection				
Written informed consent	●			
Inclusion/exclusion criteria	●			
Demographics	●			
Obtain central random number	●			
Previous history, medical history, and allergies	●			
Comorbidities and co-medications	●			
Access to internet hospital "[name]" platform	●			
Safety evaluation				
Vital signs and physical examination	●	●	●	●
Blood routine	●			●
Urine routine	●			●
Blood biochemistry testing (AST, AKP, TBIL, GGT, Cr, BUN)	●			●
Coagulation testing (PT, APTT, TT, FIB)	●			●
12-Lead ECG	●			●
Urine pregnancy test	●			●
Efficiency evaluation				
CCS Classification	●	●	●	●
Treadmill exercise test	●			●
Fasting blood glucose	●			●
Glycosylated hemoglobin	●			●
Weekly nitroglycerin dosage	●	●	●	●
Blood lipid examination (TC, TG, HDL-C, LDL-C)	●			●
Seattle angina questionnaire scores	●	●	●	●
Other jobs				
Distribute experimental drugs	●	●	●	
Recall test drug		●	●	●
Record AEs and combined medications		●	●	●
Compliance judgment		●	●	●

Abbreviations: ECG, electrocardiogram; CCS, Canadian Cardiovascular Society; ALT, alanine aminotransferase; AST, aspartate aminotransferase, AKP, alkaline phosphatase; TBIL, total bilirubin; GGT, *γγ*-glutamyl transferase; Cr, creatinine; BUN, blood urea nitrogen; PT, prothrombin time; APTT, activated partial thromboplastin time; TT, thrombin time; FIB, fibrinogen; TC, total cholesterol; TG, triglyceride; HDL-C, high-density lipoprotein cholesterol; LDL-C, low-density lipoprotein-cholesterol; AE, adverse event.

### Outcome Measures

#### Primary Outcome

In this study, the primary outcome will be graded according to the CCS classification (Sangareddi et al., 2004). We will compare the difference between the two groups in the proportion of subjects whose CCS classification decreased ≥1 after 12 weeks of medication.

#### Secondary Outcomes

The secondary outcomes of the study medication will be determined by: ◆Treadmill exercise test (conducted partially by subjects). The evaluation indexes include total treadmill exercise time, the appearance of ST-segment 1 mm depression time, the duration of exercise-limited angina, Duke treadmill score (Salokari et al., 2019), rate-pressure product, metabolic equivalents. The amounts of ST-segment deviations is defined as the maximal deviated values (mm) of ST segments on any lead.◆Fasting blood glucose and glycosylated hemoglobin (HbA1c);◆Weekly nitroglycerin dosage;◆Blood lipid examinations including total cholesterol (TC); triglyceride (TG); high-density lipoprotein cholesterol (HDL-C); low-density lipoprotein-cholesterol (LDL-C);◆Seattle angina questionnaire (SAQ) scores (Chan et al., 2014);

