### System Biological Index

Twenty subjects per group will be randomly selected for metabolomics, proteomics, and transcriptome examinations to explore the biomarkers of TJC in treating T2DM-CHD.

Blood collection requirements will consist of fasting for 10 h before sampling at study start (0 weeks) and after treatment (12 weeks), a single blood collection 5 ml, samples will be centrifuged, and serum stored in an EP tube at −70°C; Urine collection requirements will consist of fasting for 10 h before taking medicine (water is permitted), and fasting (both food and water) for 2 h before urine sampling (−1 h) to 2 h after taking the medicine, drinking water quantitatively for 2–8 h after taking the medicine, and eating low-fat meals 4 h after taking the medicine. Urine will be collected and transferred to EP tubes before taking the medicine (0 h) and after treatment (12 weeks), and kept frozen at −70°C.

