## Conclusion

This study will investigate the therapeutic potential of TJC as a combination drug. The results of the study will provide reliable clinical research evidence for the application of TJC in improving cardiac function and exercise tolerance in T2DM-CHD patients.

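### The intention-to-treat and last-observation-carried-forward rules do not fit a treadmill test done by only some subjects at two visits: a missed Week 12 test is scored as zero change

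*Protocol article*

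**What the plan says.** All references are to the protocol article.

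- **Secondary Outcomes** lists "Treadmill exercise test (conducted partially by subjects", without saying how many subjects, which ones, or when this is decided.
- **Study Procedure, Table 1** has a row "Treadmill exercise test" marked at Visit 1 and at Week 12 only. CCS class, Seattle angina questionnaire scores and weekly nitroglycerin use are marked at all four visits.
- **Statistical Analysis** states: "Data from all patients who undergo randomization will analyzed according to the intention-to-treat (ITT) principle". It adds that "the last observation carried forward method will be used for missing values". Neither rule has an exception for the treadmill test.
- **Withdrawal Criteria** include drug-related deterioration, adverse events, and early recovery with a request to stop medication.
- **Study Objectives** gives the purpose as to "evaluate the efficacy of TJC in improving cardiac function and exercise tolerance in T2DM-CHD patients", and the **Conclusion** looks forward to evidence for "the application of TJC in improving cardiac function and exercise tolerance in T2DM-CHD patients".
- **System Biological Index** defines the trial's other subset: "Twenty subjects per group will be randomly selected for metabolomics, proteomics, and transcriptome examinations".

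**The concern.** Exercise tolerance is named in the objective, the hypothesis and the conclusion, and the treadmill test is the only listed outcome that measures it by exercise testing. The stated analysis rules cannot be carried out on that outcome as intended. An all-randomised comparison needs a value for every patient, and some are never tested. With only two time points, carrying forward means substituting baseline for Week 12.

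A patient who stops because of worsening and one who stops because of recovery would, if neither has a Week 12 test, both be entered as unchanged. At stake are the size of the estimated effect on exercise tolerance, its direction if missingness differs between arms, and the population to which the conclusion applies.

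**Working it through.** **1. The plan's own figure.** The only sample size given is for the CCS primary outcome: 236 and 118, rounded to 240 and 120. With 85% against 70%, 2:1 allocation, 80% power and 0.025 per side, the unpooled formula gives for placebo (1.960 + 0.842)² × (0.70×0.30 + 0.85×0.15/2) / 0.15² = 95.5. Allowing for 20% dropout, 95.5/0.8 = 119.4, close to 118. This point does not touch that figure. No figure is given for the treadmill outcome.

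**2. What carry-forward can do here.**

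| Patient | Visit 1 test | Week 12 test | Value entered at Week 12 |
|---|---|---|---|
| Never tested | no | no | none available |
| Tested at baseline only | yes | no | baseline, so change = 0 |
| Tested twice | yes | yes | observed |

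Table 1 shows no treadmill test between these visits, so there is no post-baseline value to carry.

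**3. Size of the distortion.** Let the mean changes be a (treatment) and b (placebo), and let fractions m_T and m_P of tested patients miss Week 12. Assume that within each arm those who miss would have changed as the others did. The carried-forward estimate is (1 − m_T)a − (1 − m_P)b.

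- Equal missingness m: the estimate is (1 − m)(a − b), so the shrinkage equals m. It is nil at m = 0. At m = 0.20, the plan's dropout rate used as an assumption, the estimate is 0.80 of the true difference.
- Unequal missingness with no treatment effect (a = b = μ): the estimate is (m_P − m_T)μ. This is not zero, and its sign depends on which arm misses more.
- If missingness also depends on how the patient did, as withdrawal for deterioration or recovery would imply, the assumption above fails and the error can again go either way.

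**4. Precision in a subset.** The share tested is not stated, so the rows below are assumptions. Detectable standardised difference = (1.960 + 0.842) × √(1/n₁ + 1/n₂), at two-sided 0.05 and 80% power. The last column is the power for a difference of 0.31 SD.

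| Share tested | n₁/n₂ | Detectable | Power at 0.31 SD |
|---|---|---|---|
| All | 240/120 | 0.31 | 80% |
| Three quarters | 180/90 | 0.36 | 68% |
| Half | 120/60 | 0.44 | 51% |
| One third | 80/40 | 0.54 | 37% |
| One quarter | 60/30 | 0.63 | 29% |

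**5. Does selection break the randomisation?** That depends on when the subset is fixed. A simulation with no treatment effect (240/120, 4,000 repetitions, assumed parameters) compared two cases. A subset defined by a prognostic factor present before allocation gave 5.4% rejections and a mean bias of about 0. A subset in which testing depended on treatment as well as prognosis gave 23% rejections and a bias of about −0.18 SD. These results show the mechanism; they are not estimates for this trial.

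**The case against.** The strongest case on the other side has five parts.

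- **Randomisation may well be intact.** A reader might infer that a partly tested group is unprotected by randomisation. The documents do not support that. The first test is at Visit 1, screening examinations are done under a screening number, and the drug number goes to patients who pass screening. Staff and subjects are blinded. A subset formed by completing Visit 1 testing before the drug number is issued would remain a randomised comparison. This stands. What also stands is that Table 1 puts the treadmill test and the random number in one Visit 1 column without an order, so the point cannot be verified.
- **Table 1 is not a contradiction.** A reader might infer that it schedules everyone for the treadmill. Its marks show visits, not populations: the urine pregnancy test row is also unannotated, in a trial of men and women. This stands.
- **Detail may sit elsewhere.** The subset rule may be in the full protocol, and the analysis set may be left to the analysis plan. This stands for the missing rule, which is not the finding. It does not excuse the carry-forward rule, which the article states without exception.
- **Carry-forward from baseline affects other outcomes too.** Glucose, HbA1c and lipids are also measured only at Visits 1 and 4. True, but those outcomes are not described as done by only part of the subjects.
- **No power is claimed for the treadmill.** True. The precision table contradicts no figure in the plan; it only shows that 360 patients is not the basis of this comparison.

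**Conclusion.** The concern holds as a stated rule that misfires on this outcome. Carry-forward has nothing to enter for untested patients and can enter only baseline for those who miss Week 12. The estimated mean difference shrinks by about 20% if 20% of tested patients miss Week 12 equally in both arms and would have responded like the rest. That rate is borrowed from the sample size section and is not a treadmill figure. Unequal or response-related missingness could bias the result in either direction, by an amount the documents do not allow one to calculate. This also assumes that withdrawn patients have no Week 12 treadmill test, which the article does not say.

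Protection by randomisation within the tested set is unverified, not lost. The outcome is secondary and the hypothesis also covers cardiac function, so the point should be corrected but does not threaten the trial's main CCS result.

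**What to change.** - Define the treadmill analysis set as all randomised patients with a completed Visit 1 test dated before the drug number was issued. Recruitment has begun, but for patients already enrolled this can be identified from test dates.
- Analyse that set as randomised, adjusted for site and baseline value.
- Do not carry baseline forward for a missing Week 12 treadmill result. Use multiple imputation, which can draw on CCS class, Seattle angina questionnaire scores and nitroglycerin use, all scheduled at every visit. Add a sensitivity analysis for tests missed because of worsening, where the reason is recorded.
- Report the numbers tested per arm at Visit 1 and at Week 12.
- Limit the exercise-tolerance statement in the Conclusion to this set.

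**Cost.** No extra tests. The analysis rules can go into the analysis plan, which the article says will be specified before the final analyses. The work is a check of dates, a little more analysis, and use of recorded reasons, which may be incomplete for patients already seen. The exercise-tolerance claim becomes narrower and its precision is shown to be lower.
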